## Abstract

**Background:**

Despite remarkable medical advances in the treatment of rheumatoid arthritis (RA), a subset of patients fails to achieve complete clinical remission, as the Patient Global Assessment (PGA) of disease activity remains above 1, even after the inflammatory process is brought under control. This so-called state of ‘PGA-near-remission’ negatively impacts individuals’ functioning and potentiates inadequate care. Fatigue is a distressing and disabling symptom frequently reported by patients in PGA-near-remission, and its management remains challenging. While classic cognitive-behavioural interventions show some benefits in managing fatigue, there is potential for improvement. Recently, contextual-cognitive behavioural therapies (CCBT), like mindfulness, acceptance, and compassion-based interventions, have shown promising results in fatigue-associated disorders and their determinants. This study primarily aims to examine the efficacy of the Compassion and Mindfulness Intervention for RA (MITIG.RA), a novel intervention combining different components of CCBT, compared to treatment-as-usual (TAU) in the management of RA-associated fatigue. Secondary aims involve exploring whether MITIG.RA produces changes in the perceived impact of disease, satisfaction with disease status, levels of depression, and emotion-regulation skills.

**Methods:**

This is a single center, two-arm parallel randomized controlled trial. Patients will be screened for eligibility and willingness to participate and will be assessed and randomized to the experimental (MITIG.RA + TAU) or control condition (TAU) using computer randomization. MITIG.RA will be delivered by a certified psychologist and comprises eight sessions of 2 h, followed by two booster sessions. Outcomes will be assessed through validated self-report measures, including fatigue (primary outcome), perceived impact of disease, depressive symptoms, mindfulness, self-compassion, safety, and satisfaction (secondary outcomes). Assessment will take place at baseline, post-intervention, before the first and second booster sessions (weeks 12 and 20, respectively), and at 32 and 44 weeks after the interventions’ beginning.

**Discussion:**

We expect MITIG.RA to be effective in reducing levels of RA-associated fatigue. Secondarily, we hypothesize that the experimental group will show improvements in the overall perceived impact of disease, emotional distress, and emotion regulation skills. Our findings will contribute to determine the benefits of combining CCBT approaches for managing fatigue and associated distress in RA.

**Trial registration:**

ClinicalTrials.gov NCT05389189. Registered on May 25, 2022.

## Administrative information

Note: The numbers in curly brackets in this protocol refer to the SPIRIT checklist item numbers. The order of the items has been modified to group similar items

## Introduction

### Background and rationale {6a}

Rheumatoid arthritis (RA) is a chronic condition of unknown aetiology, characterized by pain, swelling, stiffness, and progressive disability, caused by the inflammation and gradual destruction of the synovial joints [1]. It affects around 0.5% of the adult population worldwide, being more frequent in women [2, 3], and significantly impacts several health-related domains (e.g. fatigue, sleep), affecting the individual’s functioning, well-being, and quality of life [4–6].

Current recommendations on treatment and management of RA follow a treat-to-target (T2T) approach aimed at achieving remission of the inflammatory process, or at least low disease activity, as soon and as consistently as possible [7, 8]. The guiding principles include regular quantitative assessments of inflammatory activity and consequent adjustment of immunosuppressive medication to ensure persistent clinical and analytical remission [8]. The definitions of remission currently endorsed by the American College of Rheumatology (ACR) and the European Alliance of Associations for Rheumatology (EULAR) [9], are based on tender and swollen joint counts, acute phase reactants, and the patients’ global assessment of disease activity (PGA), with or without the physician’s global assessment [9].

Due to advances in pharmacological treatments and the implementation of the T2T approach, remission has become a feasible and rather frequent outcome in RA [10]. However, about one-third of all patients with RA fail to achieve a complete remission status according to the Boolean definition endorsed by ACR and EULAR, despite the absence of inflammation, solely due to the PGA score (> 1), a status coined ‘PGA near-remission’ [11–13]. This condition entails an elevated risk of overtreatment if current recommendations are strictly followed [14–16]. These patients’ conditions cannot be improved by additional immunosuppression, as the disease process is already under control. Instead, they require adjunctive measures designed to address the mechanisms underlying the unabated PGA, with emphasis on fatigue [12].

Published reports suggest that pain, functional impairment, fatigue, and comorbidities (e.g. depression and anxiety) are the major determinants of PGA [12, 13, 17], especially after remission of the inflammatory process has been achieved [12, 17]. In this sense, PGA is primarily a measure of disease impact, i.e. a mirror of current somatic symptoms and functional impairment, rather than a reliable reflexion of inflammatory activity [12, 17].

These observations support the proposal for a dual target strategy in the management of RA [16] whereby a specific target focused on the patient’s experience of the disease would be pursued in parallel with the current one, defined by disease remission, sharpened by the exclusion of PGA.

In RA, more than 70% of patients report levels of fatigue that are similar to those observed in chronic fatigue syndrome [18], and half of all patients report it as severe and of the highest priority in their list of persistent complaints [19]. These observations are similar among patients in PGA-near-remission despite being virtually devoid of joint inflammation [12]. Patients often consider that this symptom is unduly ignored by clinicians [20].

Multiple factors have been associated with fatigue observed in RA [21], reinforcing its complex and multicausal nature [22]. Depression, disability/inactivity, and sleep disturbances seem to be key drivers of fatigue [23], whereas pain and disease activity appear to play a rather minor role [22]. This complexity underlies the major challenge faced so far in the design and implementation of effective interventions.

Adjunctive non-pharmacological interventions, including exercise, counselling, occupational therapy, cognitive behavioural therapy (CBT), and other psychological interventions, have been associated with positive results [24–26]. CBT is the gold standard intervention in many mental and physical health conditions, and a valuable intervention in RA [27–29], with proven beneficial effects in chronic pain, sleep difficulties, fatigue, self-management, self-care, coping, and well-being, both in individual and group settings [30].

Lately, contextual CBT interventions, such as mindfulness, acceptance, and compassion-based approaches, have equally been showing promising results [31, 32]. These types of interventions promote the establishment of a different relationship with internal experiences (e.g. cognitions and emotions) and the body, variables of vital importance in the experience and management of RA [33]. Preliminary evidence suggests that mindfulness-based interventions may help improve RA-related outcomes and associated psychological distress [31, 34, 35]. Regarding acceptance and commitment therapy (ACT), studies have found it effective in enhancing the quality of life [36]; improving chronic illness-related symptoms, such as pain, depression, and anxiety [37–39]; and decreasing fatigue levels in chronic fatigue syndrome [40]. ACT has also been shown to implicitly promote self-compassion (e.g. a warm and compassionate stance towards oneself in the face of setbacks [41], a recognized buffer against depression and negative pain-related outcomes [42]). Although CBT and ACT differ in their philosophical stance and therapeutic techniques [43, 44], they can be integrated in a coherent way in order to target different processes (i.e. pain, sleep disturbance, emotion dysregulation, psychological and behavioural inflexibility, functional impairment) underlying the maintenance and exacerbation of physical and mental symptoms, including fatigue, in RA [45]. The integration of traditional CBT and mindfulness, acceptance, and compassion-based approaches reflects the expansion of the field, in the face of cumulative evidence, the inclusion of both change-oriented and acceptance-oriented strategies in context-sensitive approaches, and follows efforts to optimize existing CBT protocols to favour or improve treatment response [46]. In addition, a combination of different contextual cognitive-behavioural interventions, such as those included in the MITIG.RA programme (i.e. mindfulness, acceptance, and compassion-based strategies), have been previously proposed and tested in people with binge eating disorder [47], cancer [48], chronic pain [49], and overweight and obesity [50]. Overall, these studies have shown promising results in improving disease-specific symptoms, emotional distress, cognitive and emotional regulation, healthy behaviours, social functioning, and quality of life.

The intervention and therapeutic techniques used in this study are feasible, accepted, and validated in online environments [51–53] and reveal encouraging outcomes in other chronic illnesses [42, 48, 53]. The researchers combine distinct evidence-based therapeutic components in a complementary and coherent way to target relevant processes at play in RA with the objective of alleviating fatigue in patients with this condition.

### Objectives {7}

The primary aim of the study is to investigate the impact of the programme Compassion and Mindfulness Intervention for RA (MITIG.RA) in RA-associated fatigue in comparison with treatment as usual (TAU).

Secondary aims include the effects the intervention has upon the patient’s satisfaction with disease status, overall perceived impact of disease, depression and anxiety levels, psychological flexibility, and self-compassion skills.

### Trial design {8}

The MITIG.RA is a two-arm parallel superiority randomized controlled trial. Participants will be randomized (1:1) into one of two conditions: the experimental condition (MITIG.RA programme plus TAU) and the control condition (TAU only). The first version of the protocol was registered in ClinicalTrials.gov (NCT05389189) in May 2022, before the enrolment of patients. This protocol was written in accordance with the Standard Protocol Items: Recommendations for Interventional Trials (SPIRIT) guidelines. The Consolidated Standards of Reporting Trials (CONSORT) guidelines will be followed when reporting the results of the study.

## Methods: participants, interventions and outcomes

### Study setting {9}

The study is conducted in the Rheumatology Department at Centro Hospitalar e Universitário de Coimbra, an academic rheumatology department in a Portuguese tertiary hospital.

### Eligibility criteria {10}

Participants will be recruited among adult patients with RA followed in the Rheumatology Department at Centro Hospitalar e Universitário de Coimbra.

All consenting patients will be clinically evaluated by the rheumatologist of the research team and fill out the Rheumatoid Arthritis Impact of Disease score (RAID) [54, 55] and the Patient Experienced Symptom State (PESS) [56, 57] to ascertain eligibility.

For patients to be eligible to participate in this study, they must meet the following inclusion criteria: (a) age between 18 and 65 years, (b) meet the 1987 ACR [58] or 2010 ACR/EULAR [59] classification criteria for RA, (c) be currently in PGA-near-remission (as defined by tender and swollen 28 joint counts and CRP (mg/dL) ≤ 1 and a PGA value > 1), (d) a score in the domain fatigue of the ≥ 3, (e) a PESS rating < ‘good’, and (f) under stable medication (at least 3 months).

Participants will be excluded from the study in case they present one or more of the following criteria: (a) less than 6 years of formal education; (b) unable to attend Zoom meetings unaided; (c) unable to complete self-report measures unaided; (d) presence of pain-related comorbidities (e.g. fibromyalgia or osteoarthritis); (e) presence of other comorbid medical conditions that may cause fatigue, such as anaemia (Hb < 10 mg/dL), uncontrolled hypothyroidism, or cancer; (f) presence of severe psychological symptoms or disorders (e.g. psychosis, severe depression, substance abuse); (g) currently undergoing psychological or formal psychiatric treatment; (h) pregnant patients; (i) presence of high levels of disability (advanced articular/bone erosion); and (j) inability or refusal to provide informed consent. Those who decline to participate will be inquired about the underlying reasons.

### Who will take informed consent? {26a}

The potentially eligible patients will be contacted by the research nurse who will explain the study and invite them to participate. Willing patients will receive the informed consent form with detailed information and will have the opportunity to clarify any issue with the rheumatologist from the research team to ensure a full understanding of the entire clinical trial. Only patients who are freely willing to participate and sign the written informed consent will be recruited. Participant’s written consent will be obtained prior to any study procedures.

### Additional consent provisions for collection and use of participant data and biological specimens {26b}

This trial does not involve collecting biological specimens for storage. There are no ancillary studies that require additional consent provisions.

### Interventions

#### Explanation for the choice of comparators {6b}

All patients will be treated with the standard of care (TAU). The difference between arms will be the addition of the Compassion and Mindfulness Intervention for RA.

#### Intervention description {11a}

Development of the intervention the MITIG.RA programme follows the Medical Research Council’s (MRC) framework for the development of complex interventions, last updated in 2019 [60] and was developed by a multidisciplinary team with clinical and academic experience in RA, composed of rheumatologists, nurses, and psychologists. MITIG.RA design was informed by existing protocols of individual and hybrid mindfulness, acceptance, and compassion-based interventions [42, 49] and on the RAFT study [61].

The experimental intervention, described below, will be delivered in a group format, online, for eight consecutive weeks, followed by two booster sessions after 4 and 12 additional weeks.

#### Intervention content

The MITIG.RA programme incorporates the following key topics during the 8 weeks of intervention (1st phase):(i)Psychoeducation on RA, sleep hygiene, exercise, and general nutritional recommendations (promote behavioural change and self-care, boost the sense of self-worth and self-efficacy)(ii)Activity engagement and pacing(iii)The functioning of the mind and its problematic patterns(iv)Focusing on the ‘here and now’ (mindfulness)(v)Learning new ways of self-relating—self-compassion(vi)Making room for suffering (acceptance)(vii)Moving towards what matters (identification of valued life directions and promotion of consistent values and goal-directed behaviour)(viii)Promote the implementation of the learned competencies in everyday life; identify and deal with future setbacks

The booster sessions, at 4 and 12 weeks after completion of the first phase, will focus on the revision of previously learned concepts, evaluation of potential barriers/difficulties encountered, strategies employed to deal with them, and clarification of any impending question. They will also revisit and reinforce the continued practice of mindfulness, acceptance, and compassion exercises as daily practices.

An overview of the intervention is provided in Table 1.

**Table 1 Tab1:** Intervention overview

Session	Module	Content and learning objectives
**Session 1**	Psychoeducation	• Introduction to the programme: goals, overview, and ground rules
		• Participants’ presentation, motivations to participate, and expectations about the intervention
		• Identification of current difficulties in dealing with fatigue, prior coping attempts, and their costs-benefits—creative hopelessness
		• Psychoeducation about RA and fatigue (e.g. ‘drivers’ and ‘feeders’ of fatigue)—the importance of healthy lifestyle habits (sleep hygiene, physical activity, stress, and pacing)
**Session 2**	Psychoeducation and mindfulness skills development	• Psychoeducation about the body-mind link, the function of the mind, and its patterns
		• Promoting mindfulness skills and body awareness • Introducing mindfulness in daily life:
		• informal practice
**Session 3**	Mindfulness skills development	• Promoting mindfulness skills and body awareness
		• Interoceptive exposure
		• Get to know your ‘judgy’ mind
**Session 4**	Promoting acceptance	• Control as a never-ending source of suffering
		• Learning to ‘unhook’ and making room for discomfort
**Session 5**	Self-compassion	• Cultivating compassion towards others, with a special focus on kindness
		• Compassion from others: an ally or an enemy?
		• Exploring new ways of communicating effectively
**Session 6**	Self-compassion and loving kindness	• What is compassion got to do with it—compassion flows and compassion towards the self
		• Bringing compassion to the body
		• Fostering a different form of self-self and self-other relating
**Session 7**	Values and committed action	• Living a meaningful life (values work, identification of ‘drainers’ and ‘energizers’, values-based goals setting)
		• Step-by-step action planning
		• Identification of barriers and facilitators to committed action (reinforce the importance of pacing)
**Session 8**	Closing session	• Review of the key concepts and take-home messages
		• Identification and discussion of potential setbacks and strategies to deal with them
		• Feedback on the intervention and progress made attending to the initial expectations
**Follow-up after 2 and 4 months**	Booster sessions	• Refreshment of the main concepts; evaluate difficulties in the implementation and/or practice of learned skills; revisit and consolidate mindfulness, acceptance, and compassion exercises from the sessions

#### Implementation

A board-certified clinical psychologist with training in contextual approaches will implement the protocol, following the intervention manual. The facilitator will be provided with peer supervision during the implementation of the intervention. The intervention will be implemented in groups of 10 RA patients in 8 × 2 h weekly sessions, followed by 2 × 2 h Zoom booster sessions after 4 and 12 weeks post-intervention. The sessions will be held in private Zoom conferences, allowing the participants to interact and collaborate.

Each session will employ group dynamics, visual aids, comprehensive metaphors, complementary e-books, and experiential exercises. All sessions will follow the same general structure: they will open with a gentle grounding exercise, followed by a brief review of the proposed weekly assignment (feedback, difficulties, and comments on the practices). Then, the main session’s theme and underlying concepts are introduced, followed by the practice and sharing and discussion of the guided experiential exercises. The session closes up with a brief exercise.

The implementation and consolidation of learned strategies in daily routines and practices will be regularly encouraged and monitored. Supporting audio materials featuring guided exercises will be provided for this purpose. A logbook will be used for participants to register notes, homework, and exercises and to promote consciously driven and goal-oriented behaviour.

To be considered an ‘intervention receiver’, each participant will be required to have attended, at least, the first session of the intervention. Participants attending a minimum of 6 sessions will be considered completers. Reasons for drop-out will be assessed and registered whenever possible.

#### Fidelity assessment

Intervention delivery will be performed through online group sessions using an online platform. The presence of patients in the sessions will be registered and rated for fidelity. An ‘effective’ fidelity rate has not yet been established; however, we assume that attending at least 6 sessions is likely to be adequate.

#### Treatment as usual (TAU)

All participants will benefit from the usual standard care in accordance with the current practice at the participating centre, respecting international recommendations for the management of RA. Treatment as usual consists of regular appointments with the accompanying care team, mainly involving disease assessment, treatment adjustments, and lifestyle recommendations. The usual care may include, according to the caring physician’s orientation, treatment of comorbid conditions such as, for instance, depressive or insomnia-related symptoms with the use of antidepressants and benzodiazepines. All medications and adjunctive therapies will be registered at baseline and at each visit during the study period.

#### Criteria for discontinuing or modifying allocated interventions {11b}

Patients who started psychological support outside of the study will discontinue the trial. Patients in the intervention group reporting severe adverse events or experimenting a severe worsening of their clinical condition will discontinue the study and be referred for additional treatment.

Participants may choose to stop participating in the intervention or study for any reason and will be informed on the permission, consent, and assent forms that they can choose to stop participating in the study at any time without consequence.

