### Outcomes {12}

#### Primary outcome

The following is the primary outcome:Fatigue: Fatigue levels will be assessed by the 0–10 numerical rating scale assessing fatigue as part of the RAID [54], described below. Changes at the 3-month follow-up after the second booster session, i.e. 32nd week will be considered.

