#### Sample size {14}

The primary outcome of the study will be the difference in fatigue scores between the two intervention groups at week 32, controlling for baseline values. Based on the minimum clinical improvement established for RAID score and on our previous study assessing the responsiveness of RAID.7i, we expect a minimum difference in fatigue scores between the two groups of at least 3 points [54, 71, 72].

A sample size of 91 was indicated by G*Power for analysis of covariance (ANCOVA) [*α* = 0.05, 90% statistical power, effect size of 0.50]. Assuming a 30% attrition rate and rounding up for convenience, we plan to recruit a total of 120 participants (60 participants per arm).

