## Statistical methods

### Statistical methods for primary and secondary outcomes {20a}

Descriptive analysis and test differences will be used to compare the baseline demographics and participants’ characteristics as well as variables of interest, such as participant’s dropout rates, reasons for dropout, and the presence/absence and severity of negative effects.

An intention-to-treat analysis will be conducted whenever possible and complemented with per-protocol analysis if needed.

Preliminary analyses will be conducted to guarantee that the necessary assumptions for the following tests are met. Analysis of covariance (ANCOVA) will be used to assess between-group differences in fatigue scores (the primary outcome) at the 3-month follow-up after the second booster session (32nd week), controlling for baseline values. The same analytic procedure will be used to examine the between-group differences in perceived disease activity, depression, mindfulness, and self-compassion (secondary outcomes) in the 32nd week. All effect sizes will be reported.

Additionally, time × group interaction effects on fatigue levels, perceived disease activity, depression, mindfulness, and self-compassion scores across the different time points will be tested via repeated measures analysis of variance (ANOVA), within-between interaction (with Bonferroni correction).

Potential predictors of treatment response (e.g. sociodemographic factors, baseline levels of fatigue, disease impact, depression, and anxiety) will be explored through regression analyses.

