### Methods in analysis to handle protocol non-adherence and any statistical methods to handle missing data {20c}

Missing data analysis will be performed to determine the presence and level of randomness of missing data. Multiple imputation will be used to handle the missing data [73].

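### The discontinuation rules end study participation, one of them in the intervention arm only, so week-32 fatigue would be missing in a way that is related to outcome and differs by arm

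*Protocol article*

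**What the plan says.** Protocol article, Criteria for discontinuing or modifying allocated interventions {11b}, contains two rules that end participation:

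- Intervention arm only: "Patients in the intervention group reporting severe adverse events or experimenting a severe worsening of their clinical condition will discontinue the study".
- Either arm: "Patients who started psychological support outside of the study will discontinue the trial".

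The next paragraph of {11b} lets participants leave the intervention or the study, so the text does distinguish the two. Both rules name the study or the trial.

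Plans for assessment and collection of outcomes {18a} says that what is assessed, and when, is similar in both groups, with online questionnaires at baseline and weeks 8, 12, 20, 32 and 44. Sample size {14} fixes the primary comparison: "The primary outcome of the study will be the difference in fatigue scores between the two intervention groups at week 32, controlling for baseline values". On the analysis, {20a} says "An intention-to-treat analysis will be conducted whenever possible and complemented with per-protocol analysis if needed" and {20c} says "Multiple imputation will be used to handle the missing data".

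**The concern.** Followed as written, an intervention patient who worsens severely in week 15 gives no week-32 fatigue score, while a TAU patient with the same course does. If severe worsening goes with higher fatigue, poor scores go uncollected in one arm only. Departures for outside psychological support are also likely to be related to distress, and may be commoner in the arm that is offered no psychological care.

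This is a stated follow-up rule, not a detail left to an analysis plan. No later analysis plan can recover scores that were never collected. At stake is the estimate of a self-reported primary outcome ("Fatigue levels will be assessed by the 0–10 numerical rating scale assessing fatigue as part of the RAID") in a trial whose participants know their allocation.

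**Working it through.** **Inputs from the protocol.** Allocation: "Participants will be randomized (1:1) into one of two conditions", with 60 per arm. Primary analysis: ANCOVA of week-32 fatigue on arm and baseline. Fatigue is also scored at weeks 8, 12 and 20. Assumed attrition is 30%, or 0.30 × 60 = 18 per arm, from all causes. The protocol gives no figure for withdrawals under {11b}, so it has no figure of its own to reproduce here.

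**Assumptions.** No true effect; baseline to week-32 correlation ρ = 0.5; share q of the intervention arm withdrawn for worsening, 2% to 15%; correlation r between the withdrawal trigger and the baseline-adjusted fatigue outcome, 0.3 to 1.0; SD of 2 to 2.5 points for conversion to the 0-10 scale.

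**Step 1: worsening rule alone, complete cases.** In SD units, week-32 fatigue is y = ρb + √(1−ρ²)e, where b is baseline. An intervention patient is withdrawn when a trigger w, correlated r with e, exceeds z(1−q). The mean of w among those who stay is −φ(z(1−q))/(1−q), so

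bias = −r × √(1−ρ²) × φ(z(1−q))/(1−q), with √(1−0.25) = 0.866.

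Example, q = 10% and r = 1: 0.866 × 0.1755/0.90 = 0.169 SD in favour of MITIG.RA. The simulation used 3,000 trials per setting.

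| q | Patients of 60 | φ/(1−q) | Formula, r = 0.3 to 1.0 (SD) | Simulated (SD) | False positives favouring MITIG.RA (nominal 2.5%) |
|---|---|---|---|---|---|
| 2% | 1.2 | 0.049 | 0.013 to 0.043 | 0.014 to 0.043 | 2.6% to 4.1% |
| 5% | 3 | 0.109 | 0.028 to 0.094 | 0.026 to 0.096 | 3.3% to 8.9% |
| 10% | 6 | 0.195 | 0.051 to 0.169 | 0.055 to 0.168 | 5.2% to 18.8% |
| 15% | 9 | 0.274 | 0.071 to 0.238 | 0.072 to 0.236 | 6.2% to 33.4% |

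With r = 0 there is no bias. In points, the upper end at 5% is 0.10 × 2 to 2.5 = 0.20 to 0.25. At 10% it is 0.17 × 2 to 2.5 = 0.34 to 0.43. The protocol expects a difference of at least 3 points.

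**Step 2: with imputation.** Missing week-32 scores in the intervention arm were predicted by regression on baseline and one interim score, fitted in that arm (interim to week-32 correlation 0.6, assumed). The table gives the bias in favour of MITIG.RA, in SD.

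| q | Worsening seen in the interim score: complete case / imputed | Not seen there: complete case / imputed | Share left when not seen |
|---|---|---|---|
| 2% | 0.020 / 0.000 | 0.047 / 0.038 | 81% |
| 5% | 0.044 / 0.001 or less | 0.101 / 0.083 | 82% |
| 10% | 0.079 / 0.001 or less | 0.174 / 0.146 | 84% |
| 15% | 0.112 / 0.001 | 0.240 / 0.204 | 85% |

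**Step 3: removal from both arms.** With q = 10% and r = 0.5, removal from the intervention arm only gives 0.09 SD and 7.3% false positives. The same removal in both arms gives 0.00 SD and 2.4%. The difference between arms drives the bias, so outcome-related losses from TAU under the outside-support rule would pull against those under the worsening rule. The protocol gives no figures from which to net the two.

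**The case against.** The strongest reply has five parts.

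1. **Direction.** A reader might infer that the week-32 comparison is biased in favour of MITIG.RA. That does not follow. If distressed TAU patients leave for outside support, poor outcomes leave the control arm too. This stands: only the worsening rule taken alone has a clear direction.

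2. **Deletion.** A reader might infer that the worst outcomes are deleted, or that intention-to-treat cannot be done for these patients. Planned multiple imputation keeps them in such an analysis, and the scores at weeks 8, 12 and 20 can inform it. This stands, within limits: imputation works only if the worsening is visible in fatigue scores recorded before withdrawal.

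3. **Harm.** A reader might infer that the rule hides harm. The protocol records adverse events by type, duration, frequency and relation to the intervention (Secondary outcomes). It compares dropout rates, reasons and negative effects ({20a}), and commits to evaluating and reporting unfavourable events ({22}). This stands; the loss concerns the efficacy comparison.

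4. **Size.** The trigger is a severe adverse event or clinical worsening, not fatigue, so r = 1.0 is a worst case. Section {22} anticipates no adverse events. At 2% withdrawn the bias is negligible. This stands, and is why a range is given.

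5. **SAP material.** A sensitivity analysis with worse imputed values is commonly left to an SAP. That also stands, and it is not part of the finding.

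None of this removes the core. The rule is explicit, has no TAU counterpart and ends study participation.

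**Conclusion.** The concern holds in conditional form. As written, {11b} leaves week-32 fatigue uncollected for patients selected by their clinical course, under rules that differ by arm. That sits badly with {18a} and with the intention-to-treat aim in {20a}. The worsening rule alone may favour MITIG.RA by about 0.01-0.04 SD at 2% withdrawn, 0.03-0.10 SD at 5% and 0.06-0.17 SD at 10%, before imputation. After imputation the bias is between about zero and some 80-85% of the complete-case value, depending on whether the worsening was recorded in time. These figures rest on an assumed baseline correlation of 0.5, trigger correlations of 0.3 to 1.0 and withdrawal shares that the protocol does not give. The net direction across both rules is not established.

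**What to change.** Leave the clinical rule as it is and reconcile {11b} with {18a} and {20a}:

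- Separate discontinuation of the allocated sessions from discontinuation of data collection.
- In both arms, keep sending the planned online questionnaires to week 44 after any stop, referral or start of outside support, unless consent is withdrawn.
- For the primary outcome, analyse all randomised patients as allocated, without the condition attached to intention-to-treat in {20a}.

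A sensitivity analysis giving worse values to those who stopped after worsening is optional and can go in the SAP.

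The cost is protocol wording. The questionnaires are online and nurse reminders are already planned ({11c}, {18b}), and Trial status reports that no patient had been enrolled. The downside is one of interpretation: the estimate becomes a treatment-policy one that includes the effect of outside support or additional treatment.
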